## Abstract

Tuberculosis (TB) caused 1.5 million deaths in 2020, making it the leading infectious killer after COVID-19. Bacille Calmette-Guerin (BCG) is the only licensed vaccine against TB but has sub-optimal efficacy against pulmonary TB and reduced effectiveness in regions close to the equator with high burden. Efforts to find novel vaccines are hampered due to the need for large-scale, prolonged, and costly clinical trials. Controlled human infection models (CHIMs) for TB may be used to accelerate vaccine development by ensuring only the most promising vaccine candidates are selected for phase 3 trials, but it is not currently possible to give participants
*Mycobacterium tuberculosis* as a challenge agent.

This study aims to replicate and refine an established BCG CHIM at the Liverpool School of Tropical Medicine. Participants will receive an intradermal injection with licensed BCG vaccine (Statens Serum Institut strain). In phase A, participants will undergo punch biopsy two weeks after administration, paired with minimally invasive methods of skin sampling (skin swab, microbiopsy, skin scrape). BCG detection by classical culture and molecular methods will be compared between these techniques and gold standard punch biopsy. Techniques meeting our pre-defined sensitivity and specificity criteria will be applied in Phase B to longitudinally assess intradermal BCG growth two, seven and fourteen days after administration. We will also measure compartmental immune responses in skin, blood and respiratory mucosa in Phase B.

This feasibility study will transfer and refine an existing and safe model of BCG controlled human infection. Longitudinal BCG quantification has the potential to increase model sensitivity to detect vaccine and therapeutic responses. If successful, we aim to transfer the model to Malawi in future studies, a setting with endemic TB disease, to accelerate development of vaccines and therapeutics relevant for underserved populations who stand to benefit the most.

**Registration:** ISRCTN:
ISRCTN94098600 and ClinicalTrials.gov:
NCT05820594

## Introduction

In 2020 an estimated 10 million people developed tuberculosis (TB) disease and 1.5 million people died, making TB the second leading infectious killer after COVID-19. Multi-drug resistant tuberculosis (MDR TB) is a public health crisis and health security threat, only one in three people with MDR TB were able to access appropriate treatment in 2020
^
1
^. Furthermore, an average of 47% of households affected by TB face catastrophic financial costs
^
1
^. For these reasons, the WHO End TB strategy highlights the need for an effective vaccine to prevent disease as well as safer, easier and shorter treatment regimens
^
2
^. Despite this, the only currently available vaccine for prevention of tuberculosis is the 100-year-old Bacille Calmette-Guerin (BCG). BCG is effective in preventing disseminated forms of TB but has limited efficacy against pulmonary tuberculosis, the most common and contagious form of TB. Furthermore, it has reduced effectiveness in regions closer to the equator, where the incidence and burden of TB is highest
^
3–
5
^. The remains an urgent need to develop effective vaccines to prevent pulmonary tuberculosis in these high burden settings.

Multiple factors complicate the development of novel tuberculosis (TB) vaccines. Vaccine trial design is challenging due to the long period between initial infection and progression to disease and there exists a spectrum of disease between latent, incipient, sub-clinical and active disease of which different vaccines may target different stages
^
6
^. Furthermore,
*Mycobacterium tuberculosis* (
*M.tb*) is not reliably detected in clinical specimens from patients with TB creating difficulties in determining endpoints of vaccine trials, in particular as there are no established immunological correlates of protection
^
6
^. Therefore, there are currently no alternatives to large, costly randomised controlled trials, conducted over prolonged periods
^
7,
8
^. Therefore, it is important that only the most promising vaccine candidates are selected for progression to these large phase 3 trials. Controlled human infection models (CHIM) have been used to accelerate vaccine development for various infections including malaria
^
9
^ and typhoid
^
10
^. Candidate vaccines which have passed successfully through phase I trials and are in Phase 2b efficacy studies could be included in a TB CHIM, which could be designed to either measure prevention of infection (POI) or immunological endpoints. This would allow vaccine discovery to accelerate in a cost-effective manner. Similarly, a responsive TB CHIM could accelerate the development of new drugs and promote refinement of drug combination regimens.

There are current concerns in using wild type
*M.tb* as a human challenge agent given that infection cannot be reliably eradicated, treatment is prolonged with toxicities and there is a risk of relapse or recurrent infection
^
11
^. BCG contains live attenuated
*Mycobacterium bovis* which forms part of the
*Mycobacterium tuberculosis* complex and is replication competent but does not usually cause clinical TB disease in immunocompetent individuals. A recent systematic review and workshop discussion of TB CHIM in the UK and Malawi identified several CHIMs using BCG
^
11
^. Intradermal injection with BCG was associated with expected side effects following routine vaccination with no serious adverse events (SAEs) reported in any of the identified studies. Disseminated BCG-disease has been reported in infants after routine intradermal vaccination and after intravesical installation (as chemotherapy to prevent recurrences of carcinoma in situ and/or Ta/T1 papillary tumours of the bladder) but this is extremely uncommon, primarily affecting immunocompromised individuals and readily treatable using standard anti-tuberculosis therapy
^
12
^. The workshop discussion agreed that BCG was currently the preferred agent to optimise a TB CHIM as it is licensed worldwide, has a long-established safety profile, is usually selected as the control agent in novel vaccine studies, and has been reliably recovered from previous challenge models with optimised dosing.

We are working in collaboration with partners at the University of Oxford who have established a CHIM using intradermal BCG and have published several peer reviewed articles
^
13–
16
^. They found optimal BCG recovery with punch biopsies at 2 weeks post intradermal BCG injection and using three times the standard BCG dose, without additional adverse events
^
15
^. We propose to replicate and further refine this model at the Liverpool School of Tropical Medicine. The primary end point will be determination of mycobacterial recovery by injection site biopsy at 14 days. Furthermore, we aim to perform serial minimally invasive skin sampling paired with respiratory mucosal sampling to investigate and compare the immune response between these compartments using single cell techniques.

## Protocol

### Objectives and outcome measures

**
Overarching aim
**

To establish the safety and feasibility of an established BCG controlled human infection model in Liverpool, UK.

**
Specific objectives (
Table 1)
**

1.   Confirm microbiological and molecular recovery of BCG at the intradermal injection site by gold standard skin punch biopsy (punch biopsy) 14 days after challenge

2.   Confirm safety and tolerability in healthy adult participants

3.   Determine agreement between less invasive skin biopsy techniques (including swabs, skin scrapes and microbiopsy) compared to gold standard punch biopsy on microbiological and molecular recovery of BCG with an aim to employ less invasive methods within a refined protocol in future.

4.   Confirm optimal procedures to assess immune response to BCG intradermal challenge locally (skin tissue), systemically (blood) and in the respiratory mucosa (nasal samples).

**Table 1. T1:** Outcome measures: Objectives and endpoints.

	Objectives	Endpoints
**Primary**	To quantify BCG recovered from the intradermal BCG challenge site 14 days after injection	Culture and PCR quantification of BCG at intradermal challenge site by punch biopsy
**Secondary**	Confirm safety and tolerability of study procedures in participants	Actively (solicited) and passively collected data on adverse events
	Confirm agreement between BCG recovery between punch biopsy and minimally invasive skin biopsy	Pairwise comparison between culture and PCR quantification by punch and micro skin biopsy
	Confirm agreement between BCG recovery between punch biopsy and minimally invasive skin scrape	Pairwise comparison between culture and PCR quantification by punch biopsy and skin scrape
	Longitudinal quantification of BCG recovery from the intradermal BCG challenge site at 2, 7, 14, 21 and 28 days	Culture and PCR quantification of BCG at intradermal challenge site by non-invasive skin swab.
	Confirm laboratory assays for immune response to BCG at intradermal injection site	Skin biopsy cell pellet(s) examined for immune cell differentiation and antigen stimulation
	Confirm laboratory assays for immune response to BCG in systemic circulation	Immune cell activation and functional assays; and cytokine levels in blood
	Measure immune response to BCG injection in respiratory mucosa	Nasal scrape pellet and nasal lining fluid examined for cell differentiation and activation and cytokine expression

**
Study hypotheses
**

1.   We hypothesise that we will recover the BCG SSI strain by tissue biopsy 14 days after intradermal injection by both classical microbiological and molecular diagnostic techniques.

2.   We hypothesise that quantified BCG recovery (molecular techniques) by minimally invasive skin biopsy will be at least 90% as good as gold standard punch biopsy and will offer a more acceptable method for participants in the future.

### Schedule of events and procedures

**Table 2. T2:** Schedule of visits and procedures. Visit 1 may occur up to four weeks before visit 2. X: event scheduled to occur throughout the study. A: event scheduled to occur only in Phase A. B: event scheduled to occur only in Phase B. *: Timeline is approximate only, as exact timings (± time windows) of visits relate to the actual (not intended) date of the previous visit. **in a selected subset of participants only. Phase A: punch biopsy is the gold standard comparator for BCG recovery
^
15
^ but is invasive, requiring local anaesthetic and a suture to close the wound. Our aim will be to validate less invasive techniques including minimally invasive skin biopsy
^
17
^ and a skin scrape
^
18
^ in the pilot phase (n=10) of the study. Phase B (n=20): we will select the optimal minimally invasive skin technique(s) from phase A and apply these longitudinally during study visits to assess BCG growth kinetics and interrogate immune responses over time. No local anaesthetic (LA) is required for minimally invasive biopsy; LA is known to cause artefactual blunting of humoral immune responses in laboratory assays. Nasal and throat swabs will be used to exclude SARS-CoV-2 infection prior to BCG challenge on day 0 (rapid antigen test) and subsequently to check for co-existent respiratory viral infection using PCR techniques. $ If screen >7 days from BCG. Β If virtual chat. Total blood volume per visit 50ml.

Study visit		1	2	3	4	5	6	7
Study day	Initial consent	Screening	Day 0	Day 2	Day 7	Day 14	Day 21	Day 28
Time windows (days) *				±1	±2	±2	±2	±5
Consent (Written)	x	xβ						
Consent (Verbal)	x	x	x	x	x	x	x	x
Eligibility check	x							
History and examination		x						
Vital Signs		x	x	x	x	x	x	x
Urine β-HCG		x	X$					
Screen for AEs			x	x	x	x	x	x
BCG challenge injection			x					
Skin punch biopsy						X		
Skin micro biopsy ^ 17 ^			B	B	B	x		
Skin scrape ^ 18 ^						A		
Skin swab			x	x	x	x	x	x
Inspect + photograph site			x	x	x	x	x	x
Stitch removal							X	
Diary card provided			x					
Diary card collected								x
FBC		x						
Coagulation		x						
PBMCs		x		x	x	x		
Serum			x	x	x	x		
HIV serology		x						
Blood RNA			x	x	x	x		
Nasosorption			B	B	B	B	B	B
Nasal wash **			B	B	B	B	B	B
Nasal scrape			B	B	B	B	B	B
Nasal & throat swab		B	B	B	B	B	B	B

**Table 3. T3:** Clinical assessment and STOP criteria.

Clinical history and examination	STOP if unexplained or concerning findings on history or examination
Engagement with research team	STOP if the research team have concerns about participant’s ability to commit to frequent communication and safety checks
Illness during study	STOP if participant develops a medical condition or commences medication while on the study that would meet the exclusion criteria
Full blood count	STOP if Hb <10g/l STOP if total WCC <1.5 ×109/l STOP if total WCC >12 ×109/l STOP if platelets <75 ×109/l
Resting SpO _2_	STOP if < 94%

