### Study design

Prospective longitudinal controlled human infection study after intradermal injection with BCG SSI in two phases: Phase A is designed to confirm microbiological recovery and determine agreement between the current gold standard of skin punch biopsy 14 days after injection with minimally invasive biopsy techniques. Phase B is designed to refine and optimise immunological assays to measure local (using optimal minimally invasive techniques), systemic (blood) and respiratory mucosal responses to intradermal BCG injection.

**
Phase A
**

Ten participants will receive a single intradermal injection to the upper arm of BCG SSI 6–24 × 10
^5^ colony forming units in line with an optimised and established existing protocol
^
15
^. The BCG SSI strain has been chosen as the UK licensed vaccine for TB. The dose (3x higher than that used in routine vaccination) has been chosen based on study findings by Minhinnick
*et al.*
^
15
^, who demonstrated good mycobacterial recovery at this concentration with no increase in participant adverse events between the doses. Participants will be followed up longitudinally with active assessment for tolerability; adverse events; and serious adverse events. We will determine BCG SSI recovery from the intradermal injection site 14 days later by classical microbiology and molecular diagnostic techniques using gold standard punch biopsy
^
15
^ as our primary outcome measure. In parallel, and after local anaesthetic injection, we will obtain paired minimally invasive samples (skin swab, skin scrape
^
18
^ and microbiopsy
^
17
^ from the same skin site at 14 days and determine agreement of BCG SSI recovery by classical microbiology and molecular diagnostic techniques with punch biopsy

Parameters for progression from Phase A to Phase B are:

1.Participants able to tolerate study procedures2.No experimental challenge related SAE or SUSAR detected3.Confirmation of BCG recovery by classical microbiology or molecular techniques from punch biopsy at day 14 in all 10 participants who received intradermal BCG challenge4.Confirmation of BCG recovery by classical microbiology or molecular techniques from any of the minimally invasive skin sample technique (swab, scrape and microbiopsy) at day 14 in ≥9 participants who received intradermal BCG challenge.

**
Phase B
**

Twenty participants will receive a single intradermal injection to the upper arm of BCG SSI 6–24 × 10

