There is a small risk that the micro or punch biopsy site may become infected. If this did occur, treatment with antibiotics will be prescribed. The punch biopsy site will heal to form a small scar. Allergic reactions from mild to severe may occur in response to any constituent of the local anaesthetic agent – these are extremely rare.

**
Risks associated with the COVID-19 pandemic
**

To protect participants, Infection control procedures in line with the latest NHS guidance will be used throughout the study. Participants who test positive for COVID-19 at screen will be temporarily suspended from the study to reduce the risk of onwards transmission. Samples provided up to that point will be retained and participation will be continued after the isolation period as suggested by (PHE) or longer (if participant remains unwell).

If a participant does develop symptoms suggestive of COVID-19 infection they will be advised to follow the latest NHS guidance with regards to self-isolation. A clinical review by medical staff will take place in a designated ‘COVID-19’ zone to clarify whether their symptoms are related to COVID-19 infection or the BCG vaccine. This applies to the post challenge period only. A COVID-19 nasopharyngeal swab will be performed at this visit and all further participant study visits suspended until this clarified. In the event that a study participant becomes acutely unwell with COVID-19 symptoms, they will be advised to seek urgent medical attention via normal routes of healthcare.

**
Risk to participant contacts
**

Intradermal BCG administration is not associated with risk to participant contacts. Very low levels of BCG can be detected on swabbing the moist surface of the injection site, but human-to-human transmission from contact has never been reported.

**
Risk to researchers
**

Possible risks to researchers include:

Needle stick injury during venepuncture or vaccination,Biological and chemical hazards within the laboratory,Risk of COVID-19 transmission

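### Because each visit window is counted from the previous visit's actual date, deviations add up and the day-14 primary biopsy is in window from day 9 to day 19

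*Protocol article*

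**What the plan says.** Table 2 (Schedule of events and procedures) lists visits on days 0, 2, 7, 14, 21 and 28. Its time-window row allows ±1, ±2, ±2, ±2 and ±5 days for the five visits after day 0. The footnote to that row calls the timeline approximate and explains that "exact timings (± time windows) of visits relate to the actual (not intended) date of the previous visit".

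The endpoints are timed from injection:

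- The primary objective in Table 1 is "To quantify BCG recovered from the intradermal BCG challenge site 14 days after injection".
- The third criterion for moving from Phase A to Phase B (Study design) requires recovery "from punch biopsy at day 14 in all 10 participants who received intradermal BCG challenge". The fourth criterion also refers to day 14.
- A secondary objective in Table 1 is "Longitudinal quantification of BCG recovery from the intradermal BCG challenge site at 2, 7, 14, 21 and 28 days".

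The Introduction gives the reason for the time point, again counted from injection, when describing the established model: "They found optimal BCG recovery with punch biopsies at 2 weeks post intradermal BCG injection".

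The article nowhere caps the total time from injection to biopsy or ties the day-14 visit back to day 0.

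**The concern.** The schedule and the endpoint use different time origins. A reader who sees day 14 ±2 in Table 2 would take the biopsy to fall on days 12–16. Under the footnote, a biopsy well outside that range can be fully compliant and would not be logged as a deviation.

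Bacterial quantity at a fixed time after injection is the primary endpoint, and change over time is a secondary one. Uncontrolled spread in time since injection adds variation to the first and blurs the time axis of the second. A biopsy that has been taken cannot be repeated at the intended time.

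**Working it through.** The plan gives no figure for the cumulative range, so there is none to reproduce. The inputs are the nominal days and windows in Table 2 and the rule in its footnote.

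**Permitted ranges.** The nominal gaps are 2, 5, 7, 7 and 7 days. The earliest day is the running sum of (gap − window), and the latest day is the running sum of (gap + window). Day 0 is the injection and adds no drift.

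| Visit | Gap ± window | Chained, as written | Counted from injection |
|---|---|---|---|
| Day 2 | 2 ± 1 | 1–3 | 1–3 |
| Day 7 | 5 ± 2 | 1+3 = 4 to 3+7 = 10 | 5–9 |
| Day 14 (biopsy) | 7 ± 2 | 4+5 = 9 to 10+9 = 19 | 12–16 |
| Day 21 | 7 ± 2 | 9+5 = 14 to 19+9 = 28 | 19–23 |
| Day 28 | 7 ± 5 | 14+2 = 16 to 28+12 = 40 | 23–33 |

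The drift allowed at the biopsy is ±(1+2+2) = ±5 days. That gives 11 possible days instead of 5.

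**Two consequences.**

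- The day-7 and day-14 ranges share days 9 and 10, so two participants sampled on the same day after injection can be counted at different time points. Counted from injection, the day 2, 7 and 14 ranges do not overlap.
- If the day-7 visit takes place on day 4, the biopsy window is 4+5 to 4+9, which is days 9–13. If it takes place on day 10, the window is days 15–19. In both cases a biopsy on exactly day 14 would be out of window.

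**How often (illustration).** The documents say nothing about how visits scatter within their windows. Assume independent, uniform whole-day deviations: −1 to 1, −2 to 2 and −2 to 2.

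- There are 3 × 5 × 5 = 75 equally likely combinations. The counts for total drift of −5 to +5 are 1, 3, 6, 9, 12, 13, 12, 9, 6, 3, 1.
- Outside days 12–16: 2 × (1+3+6) = 20, and 20/75 = 26.7%. In Phase A that is 2.7 of 10 biopsies on average.
- Exactly day 9, or exactly day 19: 1/75 = 1.3% each.
- SD of biopsy day, chained: √(2/3 + 2 + 2) = 2.16 days. Counted from injection: √2 = 1.41 days.

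**Range under other assumptions.**

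- If deviations cluster on the target day, with weights 1:2:1 for day 2 and 1:2:3:2:1 for days 7 and 14, there are 4 × 9 × 9 = 324 weighted combinations. Those outside days 12–16 number 2 × (1+6+19) = 52, which is 16%.
- If staff hold every visit close to its nominal day, the share falls towards zero.
- A participant who is one day late at each of the three visits is biopsied on day 14+3 = 17, still in window. Persistent lateness would therefore push the share up.

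**The case against.** The strongest reply is that this is a feasibility study. Its sample size was not set for statistical significance, and its progression criteria are yes/no, with recovery by culture or molecular methods and no quantity threshold. The article gives no recovery-by-day curve, so nothing shows that a biopsy on day 11 or 17 would change detection or the decision to proceed. The footnote also states openly that the timeline is approximate. All of this stands, and it limits the weight of the point. It does not reconcile the footnote with an endpoint defined at 14 days after injection.

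The method comparison is also largely protected. Punch biopsy, swab, scrape and microbiopsy are taken from one site at one visit, so drift moves both members of each pair together. This stands too.

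A reader might infer three stronger claims that the documents do not support:

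- **That timing will differ systematically between phases or from the established model.** Both phases share the same window row and footnote, and the other model's visit windows are not in the article.
- **That COVID-19 interruptions widen the range further.** Risk assessment has "all further participant study visits suspended until this clarified" when a participant has suggestive symptoms. Such a delay can breach a window whichever date it is counted from, and it is no part of the days 9–19 calculation.
- **That biopsies on day 9 or day 19 are to be expected.** They are permitted limits, and rare even under the uniform assumption.

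**Conclusion.** The point holds as a conflict between a stated scheduling rule and the definition of the primary endpoint. The range of days 9–19 follows from Table 2 by arithmetic alone. The 27% and the SD of 2.2 against 1.4 days rest on the assumed scatter and are illustrative; the clustered pattern gives 16%, and good scheduling could bring the share near zero.

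The effect falls on the quantified primary endpoint and on the growth-kinetics time points. Its effect on BCG recovery cannot be sized from the article. This is a worthwhile correction of moderate weight, and the study does not stand or fall by it.

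**What to change.** Change the Table 2 footnote so that the research sampling windows for days 2, 7 and 14 are counted from the injection date. The biopsy window then becomes 14 ± 2, which is days 12–16, and the three ranges no longer overlap.

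Record actual days since injection for every sample, and analyse the kinetic samples on that scale, including the day 21 and day 28 swabs. This matters because, if those two visits stay chained to the one before, they still span days 17–25 (12+5 to 16+9) and 19–37 (17+2 to 25+12).

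The cost is one footnote, processed under the article's own amendment route (sponsor agreement, then ethical and regulatory approval), and a few more visits logged as out of window. No participants, visits or procedures are added. According to Study status, recruitment had not begun at submission; if that is still so, the change can cover every biopsy.
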